## Abstract

**Background:**

Most prevalent symptoms of post-COVID syndrome (PCS) are fatigue, shortness of breath, cognitive impairment, and pain. Comorbidities such as depression and anxiety are common. The diagnosis PCS is confirmed if symptoms persist for longer than 3 months and are not better explained by another medical condition. About half of the patients are still not fit for work after psychosomatic rehabilitation. From psychotherapeutic research, it is known that a relationship-based approach is decisive for treatment efficacy. Here, the patient’s expectation that the treatment will help is one central pathway that contributes to symptom reduction and an increase in quality of life. Using positive expectations, respectively, the placebo effect in medical settings has already been proven to be beneficial.

**Objective:**

Evaluation of two expectation-focused interventions for patients with PCS to optimize the rehabilitation process. The interventions aim to focus on positive expectations and imaginations. Thus, the project should lead to further improvement in the rehabilitation of patients with PCS.

**Methods:**

The study implements a 3-arm, parallel group, longitudinal non-randomized controlled, sequential cohort design. The trial is designed to estimate the effect of *1) a 3-session psychotherapeutic expectation-focused integrative, manualized intervention, and 2) a brief intervention where patients are asked to write down their expectations on their own in a journal, compared to 3) a treatment-as-usual-only control condition (usual treatment in rehabilitation, no study intervention)*. Since the predominant symptoms in PCS patients vary a lot, the Work Ability Index (WAI) is considered as a proxy for earning capacity as primary outcomes.

**Discussion:**

The analysis will provide insights into the extent to which the interventions improve PCS. This approach was chosen to enable a larger number of practitioners to provide more specific therapeutic support for patients with PCS. The study serves as proof of principle for further research and development of more effective therapies. It emphasizes the urgent need for interdisciplinary, integrative treatment and research to better understand and manage PCS.

**Clinical trial registration:**

German Clinical Trials Register https://drks.de/search/en, DRKS00034671.

## Introduction

1

According to the World Health Organization (WHO), the post-COVID syndrome refers to symptoms that persist or newly appear more than three months after a SARS-CoV-2 infection and for which there is no (better) alternative explanation (1).The post-COVID syndrome (PCS) does not manifest itself as a uniform pattern, but consists of more than 200 different symptoms. Studies show that the most prevalent symptoms are fatigue, shortness of breath, cognitive impairment and psychosomatic complaints such as depression, anxiety, pain and post-traumatic stress disorder (2–4). Meta-analyses also carve out symptoms in 30% of patients even two years after COVID-19 (5). Furthermore, in approximately 50% of patients, the ability to work is not restored to its pre-infection level after psychosomatic rehabilitation, although they still seem to benefit significantly from the interventions (6).

Organic causes for PCS symptoms are found in less than 10% of people who seek PCS consultation (7, 8). However, dysfunctional behavioral patterns such as avoidance, endurance, misattribution, irregular breathing, and deconditioning seem to play a crucial role in the development and maintenance of symptoms. This makes the disease particularly interesting from a psychosomatic perspective. Additionally, there are also indications that dysfunctional symptom expectations contribute to symptom persistence (9–11).

An integrative causal model incorporating biological, social, experiential, and psychological factors for the development of PCS has been proposed (12). Expectations play a relevant role in all factors of this model. A recent systematic review with meta-analysis (13) also reports a significantly increased risk of developing symptoms that occur after a SARS-CoV-2 infection due to pre-existing depression or anxiety disorders, underscoring the influence of the psyche in PCS.

Furthermore, some authors suggest that PCS should be considered as persistent somatic symptoms (e.g. 14). This is a collective term for symptoms that cannot be adequately explained by structural diseases or tissue damage and often defy clear classification within conventional dualistic epistemology. The lack of a sufficiently explanatory somatic pathology increases uncertainty, fear, and stigmatization in patients and contributes to fragmented, inappropriate treatment. The vulnerability-stress model is helpful for the understanding of persistent physical symptoms, in which there is an individual, complex biopsychosocial interplay of predisposing, triggering, maintaining and reinforcing factors.

The models discussed above, and the psychological comorbidities indicate the need for psychosomatic-psychotherapeutic, multimodal, interdisciplinary treatment for patients with PCS. Accordingly, the AWMF S1 guideline for the treatment of PCS in Germany points out that psychotherapy should be offered to optimize coping strategies, treat psychological comorbidity, manage pain and teach relaxation techniques, for example. AWMF stands for “Arbeitsgemeinschaft der Wissenschaftlichen Medizinischen Fachgesellschaften”, which translates to Association of Scientific Medical Societies in Germany. The AWMF S1 guideline is a clinical guideline based on expert consensus, typically used when scientific evidence is insufficient or inconclusive. It offers guidance based on expert opinions to help healthcare professionals make informed decisions in the absence of stronger evidence (15).

A recent systematic review (16) of psychotherapy in patients with PCS found positive effects on depression, anxiety, quality of life, fatigue, and pain during treatment in most studies – with ten out of twelve studies investigating multimodal therapies including psychotherapy. The only randomized controlled trial (17) reported a significant improvement (only) in fatigue with a high effect size as a result of four months of cognitive-behavioral therapy. A considerable number of psychotherapy studies in PCS are currently being conducted or prepared (e.g., 18, 19). In addition, studies in the field of rehabilitation medicine should be mentioned in this context, which confirm the positive effects of multimodal psychosomatic therapy (20, 21). Here, PCS patients seem to benefit significantly from rehabilitative, psychotherapeutic measures – including exercise therapy aimed at improving body awareness.

But what makes psychotherapy effective? In contrast to the medical metamodel, the contextual metamodel (22) describes a relationship-based, cross-methodological approach as crucial for treatment success. The three key factors of this model are the patient’s expectations, a genuine patient-therapist relationship, and specific psychotherapeutic treatment techniques. The patient’s expectation that the treatment will help is, therefore, one pathway that contributes to symptom reduction and an improvement of quality of life. The social context of treatment should be characterized by trust, understanding, and competence. Both the therapist and the patient contribute with their personal assumptions (for a deeper understanding, see 23). In addition to the therapeutic mechanism, the social connection, and the effects of the psychotherapeutic guideline procedure, creating positive expectations about the current situation and treatment is crucial.

Using positive expectations in medical settings has repeatedly been shown to be helpful (24, 25). For example, Rief et al. (26) and Auer et al. (27) have shown that “psychological preparation” using positive expectations influences health outcomes after cardiac bypass surgery: patients who have received an intervention to optimize expectations, reported an improved recovery six months after surgery with a decrease in health impairments, cardiac anxiety, pro-inflammatory cytokine concentrations, lower hormonal stress reactions, a shorter stay in hospital and an improvement of quality of life, as well as “fitness for work” (hours per working day). It is therefore clear that patients´ expectations of treatment have a significant influence on the success of interventions, regardless of the type of disease (28–30), and expectations can significantly alter the course of treatment (31). Studies even show that negative expectations can have a dysfunctional effect on the body and psyche or even promote PCS (32–34). Interestingly, Funk et al. (35) show that patients with persistent symptoms after COVID-19 gave positive feedback on an expectation management intervention in a qualitative study. This effect should also be used in our planned quantitative study.

In summary, the persistent symptoms of PCS appear to be maintained primarily by psychological mechanisms such as patient expectations. Those could be changed through targeted interventions, which in turn lead to symptom improvement. Thus, the following research questions will be examined and hypotheses were formulated:

I. Does the addition of a psychotherapeutically guided intervention aimed at optimizing realistic and optimistic expectations regarding rehabilitation result in a significantly greater improvement in Work Ability Index (WAI) scores from pre- to post-treatment compared to standard treatment alone in patients with PCS undergoing rehabilitation?

Hypothesis: It is hypothesized that patients who receive the psychotherapeutically guided intervention in addition to psychosomatic rehabilitation will show a significantly greater improvement in WAI scores from pre- to post-treatment compared to patients who receive psychosomatic rehabilitation only.

II. Does an additional simplified version of the intervention, based on the same manual as the psychotherapeutically guided intervention and in which patients work independently on their expectations, result in a significantly greater improvement in WAI scores from pre- to post-treatment compared to standard treatment alone in patients with PCS undergoing rehabilitation?

Hypothesis: It is hypothesized that the simplified and less resource-intensive intervention in addition to psychosomatic rehabilitation will show a significantly greater improvement in WAI scores from pre- to post-treatment compared to patients who receive psychosomatic rehabilitation only.

## Materials and methods

2

The protocol is based upon the SPIRIT reporting guidelines (36) and follows Allwang et al. (18) and Nickel et al. (37).

### Objectives

2.1

The aim of the study is to investigate the effectiveness of two psychotherapeutic interventions that focus on positive expectations of patients with PCS during a psychosomatic rehabilitation program compared to treatment as usual alone (usual treatment in rehabilitation, no study intervention). Psychosomatic rehabilitation for patients with PCS in Germany follows a structured, multidisciplinary approach tailored to address both the persistent physical and psychological effects of the condition. Psychosomatic rehabilitation measures are paid for by the pension insurance provider, which checks compliance with the structured treatment. Rehabilitation begins with a thorough initial examination, which includes medical examinations, psychological screening, and functional assessments to identify the full range of symptoms, such as fatigue, shortness of breath, cognitive impairment, anxiety, and depression. Based on these assessments, structured treatment is individually tailored and comprises various therapeutic components designed to promote both physical and psychological recovery. The rehabilitation program typically combines physical therapy to restore endurance and muscle strength, especially in cases of post-viral fatigue and respiratory difficulties. Psychotherapy is frequently used to treat mental health issues such as anxiety, depression, and PTSD, which are common in patients with PCS. Relaxation techniques, such as progressive muscle relaxation or mindfulness meditation, are used to reduce stress and improve overall emotional regulation. Additionally, social and vocational counseling is integrated to support reintegration into working life and everyday routines and to help patients overcome challenges related to returning to work or dealing with social interactions. The rehabilitation program usually lasts between 3 to 4 weeks with intensive daily sessions, but may be extended depending on the patient’s individual progress and needs. Throughout the process, patients are closely monitored and the rehabilitation plan is adjusted as necessary. After completing treatment, patients often continue to receive care, for example through outpatient therapies or regular check-ups, to ensure lasting recovery and treat any remaining symptoms. The holistic approach aims to improve both physical functioning and mental health, ultimately enhancing the patient’s quality of life and ability to return their normal activities.

### Study setting and responsibilities

2.2

The study was designed and is being coordinated by the Department of Psychosomatic Medicine and Psychotherapy, Ulm University Medical Center, Ulm, Germany. The institution is being advised and supported in data collection, data analysis, and reporting by the Institute for Research in Rehabilitation Medicine at Ulm University, Bad Buchau, Germany (“IfR Ulm”). The study is being conducted at the rehabilitation clinics Glotterbad, Glottertal, and Schlossklinik, Bad Buchau, Germany. All participating study therapists are psychotherapists or physicians (in training or licensed) and undergo structured training to perform the interventions according to the manual developed by the authors of the study. The training takes place in person at both study locations. The session lasts approximately 3 hours in total, including a 30-minute break. The training is conducted by a psychologist experienced in the field of placebo research (KW) and a licensed psychotherapist (LW). First, the study therapists are informed about the scientific background. Then, the study is presented and the therapist manual is reviewed together. Individual exercises are practiced in pairs. At the end of the training, the study therapists receive a detailed overview of the study design and next steps. To ensure that standard therapy and interventions are not influenced by the training of therapists, therapists are trained only before the respective intervention group. However, influence cannot be completely ruled out, as the principles of the interventions are generally known to therapists.

Regular supervision and peer consultation sessions are conducted by the Department of Psychosomatic Medicine and Psychotherapy at Ulm University Medical Center in both rehabilitation clinics.

The study is funded by the German Pension Insurance Fund of Baden-Württemberg, whose primary interest lies in maintaining and restoring patients’ ability to work. However, it has no influence on the study design, study implementation, or data analysis.

### Design

2.3

The multicenter, longitudinal, quantitative trial employs a quasi-experimental, non-randomized sequential cohort design with three arms in a real-life design. The entire project will run from January 01, 2024, until expected June 30, 2027.

### Participants

2.4

Patients with post-COVID syndrome (PCS) who are being treated at participating rehabilitation centers are included (ICD-10 codes U08.09 and U09.9; at least one persistent PCS symptom that persists for at least 12 weeks after the initial infection). Eligible patients are adults of working age, generally between 18 and 65 years old, as rehabilitation measures in Germany are financed by the pension insurance provider in order to maintain and restore patients’ ability to work. They must have sufficient knowledge of German to complete the questionnaires and understand the intervention and must be able to give written informed consent. Study participants receive comprehensive information about the study. Potential benefits and effects as well as possible side effects are explained. Additionally, participants are informed about data security and protection, and their rights as study participants. Study staff obtains written informed consent prior conducting baseline assessments. Patients with severe psychiatric conditions according to ICD-10 (e.g., psychotic symptoms, dementia/Alzheimer’s disease, known substance dependence and abuse [except nicotine]) or current suicidal ideation will be excluded. The following demographic variables are collected as part of the study: age, sex, immigration status, family/relationship status, children, place of residence (village, small town, medium-sized town, large city), level of education, occupational group, and employment.

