#### Outcomes

2.5.7

Since the predominant symptoms in patients with PCS vary considerably and the main goal of rehabilitation is to maintain or improve work ability, the Work Ability Index (WAI) is considered the primary endpoint for measuring work ability. The WAI ranges from 7 points (unable to work) to 49 points (full work ability), with higher scores indicating better subjective work ability. Consequently, increases in WAI scores reflect improvements in perceived work ability, whereas lower scores indicate reduced work ability. International studies conducted in recent years in Europe, South America, and Asia show high internal consistency between 0.72 and 0.83. The WAI also correlates highly and significantly with all scales of the Short-Form Health Survey (SF-36) and the General Health Index (r between 0.5 and 0.8) (41). It is therefore a reliable and proven tool in rehabilitation research.

Secondary outcomes include: WHO Disability Assessment Schedule 2.0 (WHO DAS 2.0), PCS symptoms (adapted Regensburg COVID documentation, ReCoRD), somatic symptoms (Patient Health Questionnaire 15, PHQ-15 and Somatic Symptom Disorder B-criteria Scale, SSD-12), depressiveness (Patient Health Questionnaire-9, PHQ-9), anxiety (Generalized Anxiety Disorder Scale, GAD-7), fatigue (Fatigue Scale for Motor and Cognitive Functions, FSMC), post-exertional malaise (DePaul Symptom Questionnaire), expectations regarding rehabilitation and its outcome (Treatment Expectation Questionnaire, TEX-Q), self-efficacy expectations (SWE), and quality of life and general health status (2 items).

In addition, personality questionnaires are used to identify correlations between personality functioning and PCS to provide patients with the best possible psychotherapeutic support in the future. The transdiagnostic personality structure (Operationalisierte Psychodynamische Diagnostik – Strukturfragebogen Kurzform, OPD-SFK) and a scale for perfectionism (Frost Multidimensional Perfectionism Scale – Deutsche Version, FMPS-D) are used for this purpose.

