### Assignment of interventions: sequential cohort design

2.6

In order to recruit enough patients within a reasonable timeframe, the study will be conducted at two locations. Due to different treatment concepts at each rehabilitation clinic, this will also increase the study’s external validity. Patients will be recruited into the two intervention groups and the control group in clusters, with a wash-out phase in each clinic. This means that only one group will be recruited and examined at a time, and the next group will only be recruited two weeks after the previous group has been fully discharged. This reduces confounding factors, such as disappointed patients in the control group talking to patients in an intervention group. The random allocation of patients is based on their start date on the rehabilitation program.

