### Trial status

2.10

Protocol version 1.0. Recruitment began in summer 2025 and is expected to be completed in summer 2026. Trial registration: The trial was registered on May 22, 2025, in the German Clinical Trials Registry (Deutsches Register Klinischer Studien; Trial-ID: DRKS00034671).

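### Cohorts recruited months apart are compared without adjustment, and time since infection, which timing can shift, is neither named as recorded nor in any stated model

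*Protocol article*

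**What the plan says.** Section 2.3 (Design) describes a "quasi-experimental, non-randomized sequential cohort design with three arms". Section 2.6 gives the order of work in each clinic: "This means that only one group will be recruited and examined at a time". It also fixes when each further cohort may start: "the next group will only be recruited two weeks after the previous group has been fully discharged". Section 2.10 gives the calendar: "Recruitment began in summer 2025 and is expected to be completed in summer 2026".

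Section 2.4 requires "at least one persistent PCS symptom that persists for at least 12 weeks after the initial infection" and states no upper limit. The patient variables in that section are introduced as demographic: "The following demographic variables are collected as part of the study: age, sex, immigration status, family/relationship status, children, place of residence", followed by education, occupation and employment. Section 2.5.7 lists an adapted COVID documentation form (ReCoRD) for PCS symptoms but does not give its items.

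Section 2.5.1 says that group membership follows only from when a patient comes to rehabilitation, and concludes that systematic differences should be minimal. The last sentence of 2.6 even calls this allocation random.

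Section 2.8.1 analyses primary, secondary and objective outcomes with 2x2 ANOVAs (time by group), each intervention against control, and the six-month data with 3x2 ANOVAs. It names no covariate. The only regressions mentioned are exploratory and concern personality measures.

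**The concern.** Within a clinic, a patient's group is fixed by the calendar period of admission. Anything that changes over that period is therefore mixed with the group effect. Section 2.5.1 uses timing as an argument for comparability, but timing is itself a way for the groups to become different.

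Time since infection is a clear example. If referrals in this period come largely from the same past infections, a later cohort has been ill for longer than an earlier one. If patients who have been ill longer gain more or less during rehabilitation, the time-by-group term picks up part of that difference. The direction is unknown, so it could hide a benefit or imitate one. The stated models cannot separate the two, and the article promises no table by which a reader could check whether drift occurred.

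**Working it through.** **1. The plan's own figure.** Section 2.5.9 gives N = 54 for a two-group, two-time-point ANOVA with f = 0.25 and power 0.95. Alpha and the correlation between time points are not stated; I assume 0.05 and 0.5. With noncentrality f² × N × m / (1 − ρ) = 0.0625 × 54 × 2 / 0.5 = 13.5, power is 0.9501, and N = 54 is reproduced. For a comparison of change scores with 27 per arm, noncentrality is d² × 27/2. Setting this to 13.5 gives d = 1.0. On these assumptions the trial is sized for a difference in change of about 1.0 SD, not 0.5 SD. Any bias should be compared with that.

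**2. Calendar distance between cohorts.** Inputs are a stay of 3 to 4 weeks (2.5.7), a wash-out of 2 weeks (2.6), and a window S from summer to summer (2.10), read as 12 months with a range of 9 to 15. I assume three cohorts of equal length that fill the window in one clinic.

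- The gap g between the end of one cohort's recruitment and the start of the next is stay plus wash-out: 5 to 6 weeks, or 1.15 to 1.38 months.
- Cohort length is L = (S − 2g)/3.
- Adjacent midpoints are L + g = (S + g)/3 apart; first and last midpoints are 2(S + g)/3 apart.

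| Window S | Adjacent cohorts | First to last |
|---|---|---|
| 9 months | 3.4 to 3.5 months | 6.8 to 6.9 months |
| 12 months | 4.4 to 4.5 months | 8.8 to 8.9 months |
| 15 months | 5.4 to 5.5 months | 10.8 to 10.9 months |

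**3. From calendar distance to drift in duration.** Mean time since infection equals mean admission date minus mean infection date. If infection dates move forward in step with admissions, drift is about 0. If they stay fixed, drift equals the whole gap in the table. The document gives no infection dates, so it does not say where between these limits the trial lies.

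**4. Which comparison is exposed.** The planned tests are each intervention against TAU. If TAU is the first or the last cohort, one comparison spans about 9 months and the other about 4.4. If TAU is in the middle, both span about 4.4. The order is not stated outright. The group numbering, and the training of therapists only before the respective intervention group (2.2), suggest TAU first. If the groups follow their numbering, FRAME against TAU has the longer gap.

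**5. From drift to bias.** The 2x2 test concerns change from T1 to T2. A duration difference that only shifts the level of the WAI cancels. Bias arises only if duration is related to change over the stay, or to change up to six months in the 3x2 analysis.

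**6. Illustration only; every input here is assumed.** Let r be the correlation of duration with WAI change, D the drift and s the SD of duration. The spurious effect in SDs of change is r × D / s. The last column is the chance of a significant result with no true effect (two-sided 5% t-test on change, 28 per arm), with r from 0.1 to 0.3 and s from 6 to 18 months.

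| Drift D | Spurious effect | Chance of significance |
|---|---|---|
| 0 | 0 | 5% |
| 4.4 months | 0.02 to 0.22 | 5.1% to 12.8% |
| 8.8 months | 0.05 to 0.44 | 5.4% to 36.6% |

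The upper end needs full drift, the strongest assumed correlation and the smallest assumed spread together.

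**The case against.** The strongest reply is that nothing shows the variable to be missing. The list in 2.4 is expressly demographic, so a clinical history item would not be in it. The adapted ReCoRD may contain the infection date, clinic records may hold it, and a journal article need not print its case report form. That stands: a reader might infer that time since infection is not collected, and the document does not support this. Nor must staff know an exact date, since a 12-week minimum can be confirmed without one.

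A reader might also take nine months as the drift in illness duration. It is a calendar distance and applies to at most one comparison with TAU. It is not a strict ceiling either, because a 15-month window gives almost 11 months.

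Duration is also only one of several things that may change with the calendar; season, staff and referral patterns are others, and adjusting for duration removes none of them. This stands too and limits what the fix can achieve. Finally, the protocol is cautious elsewhere: 2.5.3 concedes that selection bias is possible, and 3.1 calls the study a proof of principle and wishes for a later randomized trial. These general remarks do not mention differences between cohorts over time, and they do not change the argument in 2.5.1 or the models in 2.8.1.

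**Conclusion.** The point holds in a limited form. Group is confounded with calendar time in each clinic, 2.5.1 treats timing as assurance of comparability, and the stated analyses have no covariate with which to correct for it. Time since infection is touched by the eligibility rule and can be shifted by timing, yet it is not named as recorded and is in no stated model.

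The calendar gap is about 9 months between first and last cohorts and about 4.4 between neighbours, given a 12-month window and equal cohorts. Drift in duration lies between about zero and that gap. A stronger reading, that illness duration will pass for a treatment effect or will do so by a known amount, is not supported. It would need infection dates that do not move forward and a link between duration and WAI change, and the document gives neither. What can be said is that the plan as written would leave such a difference uncorrected, and that one recorded date would show whether it exists.

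**What to change.** - **Section 2.4:** state that month and year of the infection that led to the symptoms are recorded at the admission interview, where eligibility is already checked. For cohorts already recruited, retrieve the date from existing records where available. If the ReCoRD already holds it, say so.
- **Baseline table:** report months since infection by arm and clinic.
- **Section 2.8.1:** prespecify months since infection, with baseline WAI and clinic, as covariates in the T1–T2 and six-month analyses of both comparisons with TAU. In a repeated-measures model, duration must enter with its interaction with time, since a main effect alone does not adjust the time-by-group term. The unadjusted ANOVA can be shown beside it.
- **Section 2.5.1:** replace the assurance of comparability by a statement that groups differ in calendar period and that other calendar effects remain after adjustment. Bring the word random in 2.6 into line with 2.3.

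The cost is one date field, some imprecise or missing dates, and a few degrees of freedom: with 56 patients per comparison, residual degrees of freedom for a change or T2 analysis fall from 54 to 51.
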